### Study Participants

Permission will be sought from the management of each company to allow the research team to meet with the employees at the company premises. The team will meet the employees during the morning meeting to introduce the study and provide information leaflets. The team will then return on another agreed-upon day to enroll participants, collect baseline data, and carry out the workplace HIV testing. On each data collection day, all eligible employees will receive an equal opportunity to participate in the study activities. Initially, the men will receive study information as a group, followed by one-on-one eligibility assessment and subsequent recruitment.

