### Sample Size Determination

Sample size estimation is based on the primary outcome: proportion of men who take an HIV test. The main outcomes were at the participant level. Currently, approximately 55% of males in Uganda have taken an HIV test [34]. We hypothesize a 15% increase in HIV testing in the workplace HIVST group in comparison to the control group. We considered a two-sided α of .05 with a power of 80% to detect a significant change between both groups, a 1:1 allocation ratio between the intervention and control arms, a response rate of 90%, and a design effect of 1.399. We estimate a minimum total sample size of 548 participants, with 274 per arm. The proxy for design effect was picked from the proxy variable “Had taken an HIV test and obtained results in the past year” [35]. 

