#### Permitted Concomitant Interventions

In addition to HTS, security personnel in both the intervention and control arms will receive identical additional services. These services were identified through a needs assessment that was conducted earlier [32]. The findings from that study reported that both employers and employees were more willing to undergo HIV testing at the workplace if this was provided in combination with other health promotion interventions as a way of mitigating stigma. The additional package will, therefore, include the following: a blood pressure assessment, blood glucose and BMI measurements, and an RDT for syphilis. The additional package will be offered to both the intervention and control groups prior to enrollment in the study. We do not expect these concomitant interventions to affect the results of the trial.

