#### Primary Outcome Assessment

We are operationally defining uptake of HIV testing as accepting to take an HIV test from the standard-of-care services that will be offered to the control group or receiving and returning a used HIVST kit for the intervention group. The proportion of security personnel in the control group who take an HIV test will be computed by dividing the number of participants in the standard-of-care cluster who agree to take an HIV test by the total number of those enrolled in the control arm. For the participants in the intervention cluster, uptake of HIV testing will be computed by dividing the number of participants who return the used HIVST kit within 1 month from the time of the test kit distribution by the total number who enrolled in the intervention arm.

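### Primary uptake is computed among men who enrol after the arm is fixed and known to recruiters, so a consent difference between arms biases the contrast in either direction

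*Protocol article*

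**What the plan says.** - **Order of events.** Site Selection and Allocation reports, in the past tense, that Kampala was randomised to intervention and Hoima to control. Study Participants then describes recruitment: "Initially, the men will receive study information as a group, followed by one-on-one eligibility assessment and subsequent recruitment". Enrolment and workplace testing share one visit. The ethics section requires individual written consent before a man enters the trial.
- **What happens before enrolment.** Permitted Concomitant Interventions says of the extra health checks: "The additional package will be offered to both the intervention and control groups prior to enrollment in the study". In the Intervention Arm section, one step of the self-testing explanation is addressed to a potential participant, that is, a man not yet enrolled.
- **Denominator.** Primary Outcome Assessment divides the control men who agree to a test "by the total number of those enrolled in the control arm". For the intervention arm it divides used kits returned within 1 month by the men enrolled there.
- **Analysis.** Statistical Analysis applies intention-to-treat throughout, with hierarchical logistic models and individual-level covariates.

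**The concern.** Enrolling is a choice made after allocation. Because the arm is a district, recruiters cannot be unaware of it. No sentence says that the men know the test type before they consent, but the two pre-enrolment steps above make it likely. The Introduction argues that self-testing removes some of the reasons why men avoid standard testing, so willingness to enrol may plausibly differ between arms.

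If it does, the two denominators hold differently selected men. Part of any effect on acceptability then moves from the numerator into the denominator, where the primary outcome cannot see it. Intention-to-treat keeps each enrolled man in his arm but cannot restore a man who declined. Covariate adjustment uses only what is measured in men who enrolled. At stake is the size of the primary contrast and, in more extreme settings, its sign.

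**Working it through.** **Inputs from Sample Size Determination.** Control uptake: "approximately 55% of males in Uganda have taken an HIV test". Effect: "We hypothesize a 15% increase in HIV testing in the workplace HIVST group", read as 15 points (55% to 70%). Also "a two-sided α of .05 with a power of 80"%, "a 1:1 allocation ratio between the intervention and control arms" and "a response rate of 90%, and a design effect of 1.399".

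**The plan's own figure.** The two-proportion formula with continuity correction gives 176 per arm. Then 176 × 1.399 = 246.2, and 246.2 / 0.90 = 273.6, rounded up to 274 per arm, or 548 in total. This matches the article. The sample size arithmetic is not in question, and the 15% is absolute: read as relative, it would need about 904 per arm.

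**Model for the bias.** Let *p* be the share of eligible men who test in the study and *c* the share who enrol. Decliners do not test in the study, so

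uptake among enrolled = *p* / *c*.

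I take the plan's 70% and 55% as *p*. This is an assumption, but the 55% describes men in general rather than men who consented. The consent rates are also assumed; the article states only one 90% response rate.

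| Consent, intervention / control | Intervention, per enrolled | Control, per enrolled | Difference |
|---|---|---|---|
| 90% / 90% | 0.70/0.90 = 77.8% | 0.55/0.90 = 61.1% | +16.7 |
| 90% / 80% | 77.8% | 0.55/0.80 = 68.8% | +9.0 |
| 90% / 70% | 77.8% | 0.55/0.70 = 78.6% | -0.8 |
| 95% / 65% | 0.70/0.95 = 73.7% | 0.55/0.65 = 84.6% | -10.9 |

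Per eligible man the difference is +15 points in every row.

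**When the sign reverses.** 0.70/*c*(int) < 0.55/*c*(ctl) requires *c*(int)/*c*(ctl) > 0.70/0.55 = 1.27. Since *c*(int) cannot exceed 1, control consent must be below 0.55/0.70 = 78.6%.

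**Bias in favour of self-testing.** With no true effect (55% vs 55%) and consent of 80% (intervention) and 90% (control), the result is 0.55/0.80 = 68.8% vs 0.55/0.90 = 61.1%, or +7.6 points. At the planned effective size, 274 × 0.90 / 1.399 = 176 per arm, a two-sided 5% test would call this significant in about 32% of trials.

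**A softer model.** Suppose 60% of men are willing and 40% reluctant, with testing probabilities 0.85 and 0.10 in control, and 0.90 and 0.40 in intervention. Overall this again gives 55% and 70%. Let 90% of every group enrol, except that only 30% of reluctant control men do. Control uptake among enrolled is (0.6 × 0.9 × 0.85 + 0.4 × 0.3 × 0.10) / (0.6 × 0.9 + 0.4 × 0.3) = 0.471/0.66 = 71.4%, against 70.0% in intervention (-1.4 points). If 50% of reluctant control men enrol, the figures are 64.7% and 70.0% (+5.3 points).

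**The case against.** The best defence is that several stronger readings go beyond the text.

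- A reader might infer that joining the control arm amounts to accepting the blood test, so that control uptake would approach 100%. Primary Outcome Assessment counts agreeing to test separately from enrolling, and the plan itself assumes about 55% in control. That inference is unsupported.
- A reader might blame the health package, with its syphilis test, for selective enrolment. It is identical in both arms, so it offers no mechanism for a difference. It matters here only as a sign that arm membership precedes enrolment.
- A reader might expect a reversed sign. If the planned 90% response is read as control consent, reversal cannot occur under the model above.
- That the men know their arm is an inference. The flow diagram is not shown, and the full protocol may set out when the test type is disclosed.
- Eligible men are not a perfect denominator either. The one-on-one assessment also follows allocation, eligibility depends on reported testing history, and a man who declines the study may test elsewhere.
- The article commits to CONSORT reporting, under which recruitment counts may appear anyway.

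All but the last limit the claim, and I accept them. The last helps only if the counts are kept, and it leaves the estimate unchanged. None alters the order of allocation and consent, or the enrolled-only denominators, both of which the article states.

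**Conclusion.** The point stands as a conditional risk of bias in the primary estimate, in either direction. Under the assumptions shown, a 10-point consent gap moves the observed difference from +16.7 to +9.0 points when control men consent less. When intervention men consent less, it produces +7.6 points from no effect. Reversal is possible only with a consent ratio above about 1.27 and control consent below about 79%. The article gives no consent rate by arm, so neither the presence nor the size of the bias can be judged from it.

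A reader might conclude that the primary outcome must be replaced. The documents do not support going that far. Recruitment is under way, decliners' testing outside the study is unverified, and individual covariates exist only for enrolled men. The eligible-man analysis therefore belongs beside the primary result as a key sensitivity analysis.

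**What to change.** 1. At the one-on-one assessment already described in Study Participants, log by company and arm the number of men present or approached, assessed, eligible, declined and enrolled. Counting men approached matters because the assessment itself comes after allocation.
2. Add to Primary Outcome Assessment and Statistical Analysis a prespecified key sensitivity analysis of the primary outcome. Its denominator is all eligible men, with decliners counted as not tested in the study. Run it on company-level counts and show it beside the per-enrolled result. If the two disagree, limit the conclusion to consenting men.
3. Where feasible in companies not yet visited, obtain consent using arm-neutral information before disclosing the test type.

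Cost: a tally sheet and a few sentences of text. The eligible-man analysis cannot adjust for individual covariates, and decliners' testing elsewhere stays unknown. Enrolment began in February 2020, so counts may be incomplete for companies already visited; those gaps should be reported.

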#### Intervention Arm

Since 2014, the WHO has encouraged countries to implement pilot HIVST programs to evaluate this approach. We will, therefore, follow the WHO strategy on self-testing to pilot HIVST in the workplace [22] (Figure 3). The strategy steps are as follows:

Explain the HIVST procedure and how to interpret the self-test results.Demonstrate the HIVST procedure and the interpretation of the results.Provide any additional instructional materials using an HIVST video.Answer any questions raised by the potential participant.Issue the OraQuick HIVST kits for collection of a mouth swab; participants will test at home or at a venue of their choice.Participants will return the results to the trial team in one of the following ways that will be agreed upon when they receive the kit:A phone call to the study toll-free line.A picture of the test results sent via email, WhatsApp, Facebook, or another preferred social media app.Presentation of the test kit at the health facility.Participant self-reporting the results at the health facility.Provide a referral slip and further information on linking to further services for those who receive a reactive self-test result. Those who test negative will receive further information and a referral to HIV prevention services.Provide participants with a counselor’s phone number. They will be offered the option of a call-back to return the results within 3 days of testing. Participants will also be told to use this number if they have any difficulty and need support during and after testing. This is in line with a recommendation from a study in Nigeria [36], where more than half of the participants who tested HIV positive used the helpline for support.Each participant will receive a code and instructions on what to write in case he is positive and can send these results as a text message. For example, 2018-7TR9-122-S is the code for a positive reactive test, and 2018-7TR9-122-T is the code for the nonreactive test. These codes will be randomly generated for each participant to avoid coworkers being able to accidentally interpret another person’s results.Participants who do not return the HIVST results within 3 days shall be phoned. This is in line with the Ugandan Ministry of Health test-and-treat strategy [6]. They will have given prior consent to be contacted.

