### Statistical Analysis

We will use the intention-to-treat principle for all analyses. Participants’ sociodemographic characteristics will be summarized using frequencies and proportions and will be compared across the study arms. We will employ chi-square and Fisher exact tests for categorical variables as well as means and *t* tests or analyses of variance for continuous variables [41]. To avoid unit-of-analysis errors, we shall conduct analyses by allocation unit via hierarchical logistic regression models that compare the outcome between the two arms and account for clustering among the respondents. The analysis will also adjust for individual-level covariates to elicit associations between the outcomes and the covariates. This method of analysis has been selected over other methods of analyzing cluster data to avoid any ecological fallacy [42]. For the primary outcome, we will compare the proportion of participants taking an HIV test between the two arms. Secondary analyses will be conducted to compare the proportion of HIV-positive participants who become linked to care between the two arms as well as the proportion of HIV-negative participants who take up prevention services between the two arms. The statistical analysis will be performed using Stata software (version 14; StataCorp LP). Trial findings will be published following the CONSORT (Consolidated Standards of Reporting Trials) guidelines [43].

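### The primary outcome counts agreement to test in the control arm but return of a used kit within 1 month in the HIVST arm, so it is not the single outcome that was powered and will be compared

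*Protocol article*

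**What the plan says.** Primary Outcome Assessment gives this definition of uptake: "accepting to take an HIV test from the standard-of-care services that will be offered to the control group or receiving and returning a used HIVST" (that is, the self-test device). The control proportion divides the number "who agree to take an HIV test by the total number of those enrolled in the control arm"; no time window is attached. The HIVST proportion takes as its numerator "the number of participants who return the used HIVST kit within 1 month from the time of the test kit distribution", over all men enrolled in that arm.

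Two other sections treat the outcome as one quantity. Sample Size Determination: "Sample size estimation is based on the primary outcome: proportion of men who take an HIV test". Statistical Analysis: "we will compare the proportion of participants taking an HIV test between the two arms".

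Under Intervention Arm, men test away from the study team. "Participants will return the results to the trial team in one of the following ways": a phone call, a picture, showing the kit at a health facility, or self-report at a facility. A coded text message is also offered, and men who have not reported after 3 days are phoned. Secondary Outcome Assessment lists reporting of the result, by call, picture or attendance at a facility, as a separate outcome.

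**The concern.** The arms differ in three respects:

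- **Event:** agreement in control; a test done and the kit handed back in HIVST.
- **Window:** none in control; 1 month in HIVST.
- **Evidence:** consent in control; a physical object in HIVST.

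A control man who agrees but is not tested is a success. An HIVST man who tests and phones in his result, but whose kit does not reach the team in time, is a failure on the primary outcome and a success on the secondary reporting outcome. The estimated difference then combines the effect of offering self-tests with the effect of two counting rules. The planned hierarchical logistic model handles clustering and covariates. It cannot correct an outcome that means different things in the two arms.

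**Working it through.** **1. Reproduce the planned sample size.** Inputs from Sample Size Determination: control 55%, a 15% increase, two-sided alpha 0.05, power 80%, response rate 90%, design effect 1.399, 274 per arm (548 in total).

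Reading the increase as absolute (55% vs 70%, mean 0.625):

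- n = [1.960 × √(2 × 0.625 × 0.375) + 0.842 × √(0.55 × 0.45 + 0.70 × 0.30)]² / 0.15² = 162.3
- With continuity correction: (162.3/4) × [1 + √(1 + 4/(162.3 × 0.15))]² = 175.4, so 176
- 176 × 1.399 / 0.90 = 273.6, so 274 per arm and 548 in total

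The stated figure is reproduced. Without the continuity correction the result is about 253 per arm. A relative 15% (63.25%) gives 866 to 903 per arm. The arithmetic is therefore sound, and it assumes 55% vs 70% on one common outcome of having taken a test.

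**2. Effective size.** 274 × 0.90 / 1.399 = 176 per arm.

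**3. Effect of the HIVST counting rule.** Let r be the share of HIVST testers whose used kit is returned within 1 month. The document does not give r, so a range is shown. Take true testing as 70% vs 55% and, for now, assume that every control man who agrees is tested.

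Measured difference = 0.70 × r − 0.55

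Power = Φ{[d − 1.960 × √(2p̄(1 − p̄)/176)] / √[(p₁(1 − p₁) + p₂(1 − p₂))/176]}, where d is the measured difference, p₁ and p₂ are the measured control and HIVST proportions, and p̄ is their mean

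| Testers not returning the kit in time | Counted HIVST uptake | Measured difference (points) | Power to favour HIVST |
|---|---|---|---|
| 0% | 70.0% | +15.0 | 83% |
| 5% | 66.5% | +11.5 | 60% |
| 10% | 63.0% | +8.0 | 33% |
| 20% | 56.0% | +1.0 | 4% |
| 21.4% | 55.0% | 0 | 2.5% |
| 30% | 49.0% | −6.0 | 0.1% |

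The first row is 83% rather than 80% because this power formula has no continuity correction. The break-even point is 1 − 0.55/0.70 = 21.4%.

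**4. Control side.** If only 95% of control men who agree are tested (an assumption), true testing of 55% is counted as 0.55/0.95 = 57.9%. With r = 0.90 the measured difference is 63.0 − 57.9 = 5.1 points, and power is about 16%.

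**5. No true effect.** With 55% testing in both arms and r = 0.80, the measured difference is 0.55 × 0.80 − 0.55 = −11 points. The chance of a significant result favouring control is about 54%.

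**6. An opposing error.** Kits used by someone else would raise the HIVST count. At r = 0.90 the loss is 7 points. To cancel it, 0.07/0.30 = 23% of the HIVST men who did not test would have to return such a kit.

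**The case against.** Kit return is an objective and conservative measure. The Discussion names confirmation of self-reported results as a foreseen difficulty, and a used kit is physical evidence that a test was done. The article also separates reporting a result (secondary) from returning a kit (primary), and nothing says that a man who phones in does not also hand in his kit. A collection step may be described in the full protocol. On the control side, Study Participants has the team carry out workplace testing on the agreed day, the Abstract places control testing at work premises, and under Control Arm the sample is tested at once. Agreement may then be almost the same as testing.

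Much of this stands, and it rules out three stronger readings that a reader might infer:

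- **That every man using a remote channel is lost, so each 10% of users costs 7 points.** This would require that reporting remotely excludes returning the kit, which the document does not say. The 7 points apply to each 10% of testers whose kit is not returned.
- **That the net bias is known to run against HIVST.** Kits used by someone else, and perhaps the 3-day calls that only this arm receives, could push the other way. The calls are listed among the intervention steps and may be seen as part of the treatment.
- **That control uptake is materially overstated.** On-the-spot testing would make this error small. However, Control Arm also describes the care as facility-based, so agreement cannot simply be equated with testing, and those descriptions need to be reconciled.

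The objection does not remove the stated difference in event and window. Nor does it explain how a kit comes back from a man who reports by call, text, picture or word of mouth.

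**Conclusion.** The point holds. The document fixes two different numerators for its primary outcome, while it powers and compares one. As written, an HIVST man who tests and reports as told may be counted as not tested. The definitions by themselves work against HIVST; the size and sign of the net bias cannot be settled from the document. If true testing is 70% vs 55% and all control men who agree are tested, non-return of 5%, 10% or 21% of testers' kits leaves 11.5, 8 or 0 of the planned 15 points. These figures illustrate sensitivity and do not predict the return rate. The sample size calculation itself is not at fault.

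**What to change.** Use one definition in both arms: an HIV test performed within 1 month of enrolment, over all men enrolled.

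- **Control:** count tests actually carried out by the nurse or counselor, not agreement.
- **HIVST:** count a used kit returned or presented, a picture, or a result reported through one of the channels listed under Intervention Arm. State whether a result first obtained on the 3-day call counts, and flag such results.
- **Sensitivity analysis, stated in advance:** limit HIVST successes to tests verified by kit or picture, which bounds over-reporting.
- **Continuity:** report the definition now in Primary Outcome Assessment alongside.

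Recruitment began in February 2020, so make the change as a dated amendment with a registry update before any comparison by arm.

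The planned sample size need not change, because it already assumes a common outcome. The cost is that part of the HIVST numerator will rest on self-report, a source of over-reporting in one arm only, which is why the verified analysis is needed. Completed control tests must also be recorded for each man; the document names no record for this.

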#### Secondary Outcome Assessment

The following outcomes will be reported in the clinical trial record [33]:

HIV status reporting—the proportion of participants who self-report HIV test results. This will be assessed via telephone call by participants to the trial toll-free line or via picture of the self-test result sent through any of the following electronic channels: study email, WhatsApp, or the study Facebook account. Further assessment will include the presentation of either the trial participant or the self-test at a health facility.Linkage into HIV care—the proportion of participants with positive results who link to a health facility for HIV care. This will be assessed by checking the clinic records from the selected HIV care and treatment facilities at 1 and 3 months.Initiation of ART—the proportion of participants who initiate ART. This will be assessed by checking clinic records or possession of an ART card. Data will be collected using a questionnaire at 1 and 3 months.Uptake of VMMC following HIVST—the proportion of previously uncircumcised participants who self-report VMMC at 1 and 3 months.Consistent condom use following HIVST—the proportion of participants who use a condom for each sexual encounter for 1 month. Condom use will be assessed through verbal reports from the participants. Participants will be followed up at 1 and 3 months.Uptake of PrEP by men who have sex with men (MSM)—the proportion of MSM who initiate PrEP at 1 and 3 months. In this study, MSM will indicate the behaviors that transmit HIV infection, rather than how individuals self-identify in terms of their sexuality [38].

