### Study Setting

This study will be conducted in two Ugandan districts, namely Kampala, the capital city, which houses headquarters for most companies offering security services in Uganda, and Hoima, an oil and natural gas base that has several security companies. Additionally, the social and relational dynamics created by the work demands of men working in private security services have an influence on their vulnerability to HIV risk. Many of the workers migrate from their homes to work in cities, which places them at high risk of HIV, especially if they remain away from home and/or away from their regular partners for long periods [31].

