### Study Outcomes

#### Overview

The primary outcome will be uptake of HIV testing. Secondary outcomes will include testing yield, proportion of participants initiating ART during the first 3 months following HIV test results, and proportion of participants linked to prevention services (ie, consistent condom use, VMMC, PrEP, and retesting for HIV).

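### Consistent condom use is counted as linkage to prevention, but it is defined as behaviour present at follow-up, not as new uptake

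*Protocol article*

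**What the plan says.** The protocol article treats the condom item in four places.

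- **Study Outcomes, Overview.** One secondary outcome is the "proportion of participants linked to prevention services (ie, consistent condom use, VMMC, PrEP, and retesting for HIV". The list is introduced as a definition, so condom use is part of what linkage means.
- **Secondary Outcome Assessment.** The item is "the proportion of participants who use a condom for each sexual encounter for 1 month". On measurement: "Condom use will be assessed through verbal reports from the participants". On timing: "Participants will be followed up at 1 and 3 months". In the same list, circumcision is "the proportion of previously uncircumcised participants who self-report VMMC at 1 and 3 months", and PrEP is counted when a man initiates it.
- **Referral of Clients Confirmed as HIV Negative.** Condom use is offered to sexually active men. The unit of evaluation for HIV-negative men rests on facility testing, circumcision, partner services and PrEP records; condom use is not among them.
- **Statistical Analysis.** The planned comparison is of "the proportion of HIV-negative participants who take up prevention services between the two arms". The model adjusts for individual-level covariates that are not named.

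Two further sections matter. Study Participants says that baseline data are collected, without listing them. Site Selection and Allocation assigns Kampala to the intervention and Hoima to control.

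**The concern.** Linkage and take-up describe something that happens after testing. The circumcision and PrEP items respect this: each counts a new event, and circumcision is limited to men in whom it can still occur. The condom item counts everyone who shows the behaviour at follow-up, including men who had the habit before enrolment. It also has no rule for a man with no sex in the recall month: he can be said to meet the definition with nothing to count, or to fail it.

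Two consequences follow. Prior users add the same amount to both arms and shrink the contrast. And where prior use differs between the arms, that difference appears as an effect. With many randomized clusters the second problem would average out; with one district per arm it does not. At stake is the prevention part of the trial's hypothesis, not its primary question.

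**Working it through.** **1. The plan's own figure.** The documents give no expected rate, effect or sample size for the condom or prevention outcome. The only stated calculation is for uptake of testing: 55% v 70%, two-sided alpha 0.05, power 80%, with continuity correction, gives 176 per arm. Then 176 × 1.399 / 0.90 = 273.6, so 274 per arm and 548 in total, as stated. Nothing below changes it.

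**2. The definitions side by side.**

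| Item | Who can count | What is counted |
|---|---|---|
| Circumcision | previously uncircumcised men | new event |
| PrEP | the at-risk group named in the item | initiation |
| Condom use | participants, no restriction stated | behaviour over 1 month, whatever came before |

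Only the condom row measures a state and not a change.

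**3. Dilution (all rates assumed).** Let b be the share already using condoms consistently and still doing so at follow-up, and u the rate of new uptake, independent of b. If any one service counts as linkage, the measured proportion is

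p = 1 − (1 − b)(1 − u) = b + (1 − b)u.

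The same algebra describes the condom item alone, with u read as new adoption among men not already consistent users. Take u = 10% in control and 20% in the intervention arm:

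| Prior users b, both arms | Control | Intervention | Difference | Ratio |
|---|---|---|---|---|
| 0% | 10% | 20% | 10 points | 2.00 |
| 10% | 19% | 28% | 9 points | 1.47 |
| 20% | 28% | 36% | 8 points | 1.29 |
| 30% | 37% | 44% | 7 points | 1.19 |
| 40% | 46% | 52% | 6 points | 1.13 |
| 50% | 55% | 60% | 5 points | 1.09 |

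The difference is (1 − b) × 10 points throughout.

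**4. District difference (rates assumed).** No true effect, u = 10% in both arms:

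- b = 40% intervention, 30% control: 1 − 0.60 × 0.90 = 46% v 1 − 0.70 × 0.90 = 37%, a spurious +9 points.
- b = 30% intervention, 20% control: 37% v 28%, again +9. Reversing the districts gives −9.

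With a true 10-point effect and prior use of 20% in the intervention arm v 30% in control: 1 − 0.80 × 0.80 = 36% v 37%, or −1 point. That last case is chosen to oppose the effect and shows only what is possible.

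**5. Men with no sex in the month (rates assumed).** Let s be their share and q = 30% the consistent-use rate among sexually active men. Counted as meeting the definition, p = s + (1 − s)q; counted as failing, p = (1 − s)q. The gap is exactly s.

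| s | Counted as met | Counted as failed |
|---|---|---|
| 5% | 33.5% | 28.5% |
| 10% | 37% | 27% |
| 20% | 44% | 24% |
| 30% | 51% | 21% |

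**The case against.** The best defence has five parts.

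- **Comparing the prevalence of a behaviour between randomized arms is legitimate.** With balanced arms, prior use costs precision and contrast but creates no false effect. This stands. The spurious difference needs imbalance, which here comes from the one-district-per-arm allocation. That is a wider design problem, and redefining one outcome does not cure it.
- **A baseline condom question may exist.** A reader might infer that condom use is first asked after the intervention. The article does not say so: baseline data of unstated content are collected and unnamed covariates enter the model. Only the narrower statement is supported: the outcome as defined makes no use of a baseline value.
- **Abstinence is not documented.** A reader might take the Study Setting remark about men at risk "especially if they remain away from home and/or away from their regular partners for long periods" to mean that many have no sex. That sentence concerns raised HIV risk and says nothing of abstinence. The firmer support for a missing rule is that condoms are offered to sexually active men while the outcome refers simply to participants. Even that word may be shorthand, since ART initiation is worded the same way.
- **The composite is one reading.** The operational section lists condom use, circumcision and PrEP separately and states no any-of rule. If they are reported singly, prior condom use cannot mask circumcision or PrEP. The prior-user and no-sex problems then stay within the condom item.
- **Restricting to men who report sex has its own cost.** It selects on behaviour after randomization, which testing and counselling may change, and sits badly with the intention-to-treat principle stated for all analyses. This stands and shapes the fix.

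**Conclusion.** The point holds as a definition problem in one self-reported secondary outcome. The article calls condom use linkage or take-up but defines it as prevalence at follow-up, out of line with its own circumcision and PrEP items and with the record-based evaluation of HIV-negative men. Counting standing habits as linkage follows from the text as written and does not depend on what an analysis plan might add.

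The size is unknown. The 7-point and 9-point figures rest on assumed rates, on independence of prior use and new uptake, and, for the linkage outcome, on the any-of reading. They do not predict this trial's result. Nor do the documents show that the districts differ in condom use; they show only that the design would let such a difference through. The issue is minor.

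**What to change.** 1. Take condom use out of the linkage definition in the Overview and report it as a separate behavioural outcome. Alternatively, keep it there but count it only for men who were not consistent users at baseline.
2. Use a baseline answer to the same 1-month condom question as a named covariate in the hierarchical logistic model. If the question is not already asked, add it.
3. Keep all HIV-negative participants in the main analysis and report three levels at each visit: no sex, consistent use, not consistent. State in advance how men with no sex are coded in any two-level model.
4. Give the result among men reporting sex only as a supplementary analysis, labelled as selecting on post-randomization behaviour.

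The cost is revised wording and at most one baseline question. Enrolment began in February 2020 and was still open at submission, so men already enrolled may lack the baseline answer; their number should be reported by arm. Adjustment for measured prior use reduces a district difference in that habit but does not remove the confounding of arm with district.
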